#### 2.8.2. Cost Analyses

Primary cost analysis: material cost of the Libre CGM system vs. SMBG

We calculated the cost of three times daily SMBG per patient per 1 year. Assumptions to consider included provision of one glucometer per patient per year plus a replacement in up to 20% of patients in the second half of the year, batteries for the glucometer every 6 months, 3 test strips per day per patient plus 10% for supplementing those who might need additional support (such as during acute illness), 1 lancet device per patient per year with replacement of up to 50% in the second half of the year, and two packets of 200 lancets per patient per year. We also calculated the cost of SMBG six times daily per patient per 1 year, since international consensus standards state that SMBG should occur 6–10 times per day for optimum care.

We calculated the direct cost of the Freestyle Libre 2 CGM system per patient per 1 year. This model includes provision of 1 Freestyle Libre 2 CGM reader per patient including rechargeable batteries, 26 sensors per year (one every 14 days), glucose test strips for confirmation of readings four times per week (the CGM system has glucose monitoring capacity, so no separate meter is necessary), one lancet device, and 50 lancets. We assume 10% extra of these supplies for replacement or increased needs, except for sensors, where we assume 20% extra are needed.

#### 2.8.3. Secondary Cost Analyses

For each patient in each group per year, we will calculate the cost of hospital admissions for severe hypoglycemia and DKA as well as days missed from school or work. We will also estimate future long-term costs to the healthcare system. Diabetes chronic complications occur after many years of poor diabetes control and are not likely to appear during this study, although they could develop earlier in African youth with T1D because of chronic poor control. We will calculate the average health care cost in Uganda for retinopathy, renal failure, foot ulcer care, and amputation. There are good data available documenting the specific risk reductions associated with specific improvements in glucose TIR, and we will use these in our calculations. The hazard rate of development of retinopathy progression is reduced by 64% and development of microalbuminuria is reduced by 40% for each 10-point increase in glucose time-in-range [16]. Based on the literature, we expecting to achieve at least a 10-point improvement in glucose time-in-range in patients using CGM [17] and at the end of the study we will use our actual rates of improvement to calculate anticipated future risk reduction for retinopathy and microalbuminuria using published data [16].

In a study in Northern Uganda looking at disability from limb loss [18], the economic burden of being disabled was twofold—inability to work and the extra costs associated with accessing disability services in distant places. This will be a dimension which we will explore and try to cost each aspect as it affects individual patients and their households.

Summary statistics will be calculated for each cost endpoint. The primary and secondary endpoints will be compared between the CGM and SMBG groups using 2-sample *t*-tests or the Wilcoxon rank-sum tests. Linear regression models will also be used for the group comparisons with adjustment for important covariates such as age, gender, and education levels.

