### 2.3. Overview, Study Design

This randomized, non-blinded, phase 4 clinical trial is programmed as follows. Subjects are assigned 1:1 to the CGM Group or the Control Group. Randomization is stratified by clinic and by age group (4–11, 12–18, and 19–26 years) with approximately equal numbers in each age group and of the two clinic locations. The random numbers were generated by the statistician using a central computer. At baseline, a 1–2 weeks initial assessment is performed where the ability to wear and return the sensor can be demonstrated, as an entry criterion for randomization. After this, 180 children and young adults with T1D will be randomized into the clinical trial in four 12-month cohorts of 45 patients each.

The study design is shown in Figure 1. Half of the subjects (*n* = 90, CGM Group) receive unblinded FreeStyle Libre 2 CGM for the entire 12 months. Half (*n* = 90, Control Group) are given sufficient test strips for three times daily SMBG months 1–6, while wearing blinded CGM for endpoint assessment. For months 7–12 they switch to unblinded CGM. The treatment group is expected to continuously modify their insulin dose and behaviors based on real-time, continuous availability of glucose data. The control group has no access to these data and will base their actions on SMBG measurement alone. For study data analysis, we will use unblinded sensor data from the treatment group and blinded sensor data from the control group that is obtained in the two weeks preceding each monthly visit; thus, the CGM data comparison period will be the same for both groups.

The investigators and the patients are not blinded to treatment arm as there is no practical way to do this. But they are blinded to the comparison data for CGM versus SMBG use until the study is completed. Table 1 lists the schedule of study assessments.

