All patients in this study, including those in the control group, will receive more intensive education, greater attention from the diabetes team, and more test strips than are commonly available today. If this approach results in similar levels of improvement in glucose TIR in control subjects using SMBG compared to patients who use unblinded CGM, this study will have performed an important service by demonstrating that there is no need for this expensive therapy and that, instead, more focus needs to be placed on patient education and interaction with the medical team. But if CGM leads to significantly greater improvement in diabetes metabolic control by reducing hyper- and hypoglycemia, then the ethical question is not whether to provide this therapy in resource poor settings but how to make it affordable. This is similar to the issue that arose when HIV/AIDS therapies first became available. Such decisions must be guided by data obtained in the specific and unique settings found in low, low-/middle income nations. The goal of this protocol is to obtain these data.

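### Secondary cost analyses: a yearly comparison by group would mix six months of CGM into the SMBG arm, and the TIR gain behind the complication savings is not stated to be net of control

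*Protocol article*

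**What the plan says.** **Costing unit and contrast.** Section 2.8.3 of the protocol article states: "For each patient in each group per year, we will calculate the cost of hospital admissions for severe hypoglycemia and DKA". Days missed from school or work are costed on the same basis. The endpoints "will be compared between the CGM and SMBG groups using 2-sample *t*-tests or the Wilcoxon rank-sum tests", with covariate-adjusted linear regression as a supplement. No observation window is given.

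**Exposure.** Section 2.3 says that the CGM Group "receive unblinded FreeStyle Libre 2 CGM for the entire 12 months". Controls "are given sufficient test strips for three times daily SMBG months 1–6, while wearing blinded CGM for endpoint assessment". The next step is "For months 7–12 they switch to unblinded CGM".

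**Complication projection.** Section 2.8.3 takes from published work a hazard reduction of 64% for retinopathy progression and 40% for microalbuminuria per 10 points of TIR. It expects "at least a 10-point improvement in glucose time-in-range in patients using CGM" and adds that "at the end of the study we will use our actual rates of improvement to calculate anticipated future risk reduction". It does not say which arm or contrast supplies the improvement.

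**Shared co-intervention.** The Discussion notes: "All patients in this study, including those in the control group, will receive more intensive education". It also allows that controls might improve as much as CGM users.

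**The concern.** The plan fixes a unit of time (a year) and a contrast (CGM against SMBG) that its own crossover makes incompatible, because no participant spends twelve months on SMBG. A twelve-month total by group would pull the difference in admission and absence costs toward zero.

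The complication projection carries a risk in the opposite direction. If the change from baseline in CGM users is the input, improvement due to education, staff attention and extra strips in both arms is counted as a benefit of CGM.

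Cost analysis is a primary objective (Section 2.2). The abstract names hospitalizations, missed school or work and complications among its assumptions, and Section 2.9 says that the results go to the Ministry of Health for policy. Near-term savings could be understated and long-term savings overstated, and there is no reason to expect the two to cancel.

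**Working it through.** **Plan's own figures.** The article gives no expected value or power for the cost comparison. The figures that can be reproduced are the hazard reductions: 64% and 40% per 10 points correspond to hazard ratios of 0.36 and 0.60, and a 10-point gain returns 1 − 0.36 = 64% and 1 − 0.60 = 40%. The sample size is not touched by this point.

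**1. Admissions and missed days.** Let c0 be the annual cost on SMBG and c1 the annual cost on CGM, with constant rates and no carry-over.

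- CGM Group over 12 months: c1
- Control Group over 12 months: 0.5·c0 + 0.5·c1
- Difference: (0.5·c0 + 0.5·c1) − c1 = 0.5·(c0 − c1)

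This is half the annual CGM–SMBG difference, whatever the rates.

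Example in arbitrary units: 100 per half-year on SMBG and 60 on CGM.

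- True annual figures: 200 against 120, a saving of 80 (80/200 = 40%)
- Twelve-month totals by group: 160 against 120, a saving of 40 (40/160 = 25%)

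For scale, if a full year of SMBG against a full year of CGM had 80% power at two-sided 0.05, halving the difference with unchanged variance would leave about 29%; 90% power would fall to about 37%.

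**2. Complication projection.** With TIR gain g, the reduction is 1 − 0.36^(g/10) for retinopathy and 1 − 0.60^(g/10) for microalbuminuria. Take a 10-point gain in CGM users (the article's expectation) and control gains of 0 to 5 points (an assumption; the article gives none):

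| Control gain | Net gain | Retinopathy | Microalbuminuria |
|---|---|---|---|
| 0 | 10 | 64% | 40% |
| 2 | 8 | 56% | 34% |
| 4 | 6 | 46% | 26% |
| 5 | 5 | 40% | 23% |

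A projection from the within-arm gain would report 64% and 40% in every row.

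**3. Precision if only six months are used.** Take Poisson events and n patients per arm.

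- An arm's annual rate c has variance c/n from twelve months.
- From doubled six-month counts it is 4·(c/2)/n = 2c/n.
- The standard error is therefore √2 = 1.41 times as large, about 40% more.

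For the difference between arms, the variance is 2(c0 + c1)/n from the annualised six months, against (0.5·c0 + 1.5·c1)/n from the twelve-month totals.

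- With similar rates, the standard error ratio is √(4/2) = 1.41. The contrast doubles, so signal-to-noise improves by 2/1.41 = 1.41.
- In the 200 against 120 example, the ratio is √(640/280) = 1.51, and the improvement is 2/1.51 = 1.32.

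**The case against.** The strongest reply is that these are ambiguities in a condensed article.

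- **Comparator period.** Section 2.3 does name the control group's first half-year as the control, and the abstract counts the cost analysis among the primary endpoints. An SMBG group exists only in that period. This softens the point. However, the sentence belongs to a paragraph on primary endpoint assessment after six months of CGM, and nothing carries it over to event and absence costs.
- **Yearly unit.** Section 2.8.2 uses a year as a costing unit, so the yearly figure in Section 2.8.3 could be an annualised rate. That is possible, but annualised over which months is still unstated.
- **TIR input.** A reader might infer that the plan has chosen an uncontrolled gain. The documents do not say so. The wording names no arm, the 10-point figure is a literature expectation, and Sections 2.2 and 2.7 define the TIR effect between arms. The within-arm reading remains likely, because the improvement is introduced for patients using CGM and Section 2.3 describes assessment after six months of CGM in each group in turn.
- **Scope.** A reader might infer that none of the cost results compare CGM with SMBG. That is not supported. Section 2.8.2 prices a modelled full year of supplies for each method, and the crossover cannot affect it.
- **Detail left to a fuller plan.** A costing window often is left there. Here, though, the article states a unit and a contrast which, followed as written, give a diluted answer.

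**Conclusion.** The point holds for the secondary cost analyses in Section 2.8.3 only.

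For admissions and missed days, a literal twelve-month comparison by group would show about half the annual CGM–SMBG difference. The exact half rests on constant rates and no carry-over; the direction, toward zero, requires only that CGM acts in the same direction in the control group's second half-year.

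For complications, the conclusion is conditional. If the within-arm gain is used, the projection overstates what CGM achieves whenever controls also improve. With a 10-point CGM gain, a 5-point control gain would mean 40% and 23% attributable reductions where 64% and 40% are reported. The control gain is an assumed range, and the scaling treats the published reductions as multiplicative in TIR.

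**What to change.** In Section 2.8.3 or the analysis plan, state that:

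1. Admission and absence costs are compared between randomised arms over months 0–6, multiplied by two if a yearly figure is wanted, with the same window for the two-sample tests and the regression.
2. Months 7–12 are reported separately and descriptively.
3. The complication projection uses the between-arm difference in six-month TIR change, and is repeated at its confidence limits.

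The change is to wording and can be made before the cost data are analysed; last follow-up is planned for 30 April 2027. Table 1 schedules interim history, adverse events and severe hypoglycemia at every monthly visit, so admissions should be separable at month 6. Missed days are separable too if they are recorded by visit.

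The price is precision: each arm's annualised rate has a standard error about 40% larger under the Poisson assumption, and doubling presumes that the second half-year resembles the first. The undiluted contrast more than offsets the loss of precision (a net gain of about 1.3 to 1.4 in signal-to-noise in the cases above). If this is already what the sponsor intends, saying so costs nothing.

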## Abstract

Metabolic control is poor in East Africa for youth with type1 diabetes (T1D). Self-monitoring of blood glucose (SMBG) by fingerstick 2–3 times daily is routine care. This randomized controlled trial (RCT) will test the hypothesis that providing continuous glucose monitoring (CGM) to Ugandan youth with T1D will improve glucose time-in-range (TIR glucose 3.9–10.0 mmol/L) and be cost effective in this setting. Ugandan youth with T1D (*n* = 180, age 4–26 years) will be divided into four 12-month cohorts (August 2022–August 2027). Half will receive unblinded Freestyle Libre 2 Flash CGM for 12 months. For six months, control subjects received sufficient test strips for SMBG three times daily while wearing blinded Freestyle Libre Pro CGM (for endpoint assessment), and then they switch to unblinded CGM for six months. Everyone receives monthly diabetes education. The primary endpoints are as follows: (1) the six-month change from baseline in glucose TIR, unblinded CGM versus SMBG; (2) a cost analysis of CGM versus SMBG. The TIR hypothesis will be tested by linear mixed effects models. Cost analysis assumptions include direct material and indirect costs like hospitalizations, missed school/work, and diabetes complications. The study will inform T1D management guidelines in a low resource setting using evidence-based recommendations.

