## Figures and Tables

**Figure 1 mps-09-00043-f001:**
[figure not shown]
Study flow diagram figure legend. Dark green color is librepro wear for 2wks, yellow is unblinded CGM wear, blue is for Blinded CGM wear.

**Table 1 mps-09-00043-t001:** Overview of patient schedule activities.

Time (−1 Week, then Monthly)	−1 wk	0	1	2	3	4	5	6	7	8	9	10	11	12
Visit Number	1	2	3	4	5	6	7	8	9	10	11	12	13	14
**Informed Consent/Assent**	X													
**Initial Eligibility Screening, including wearing a single blinded Libre Pro CGM for at least 7 days**	X													
**Final Eligibility, Randomization**		X												
**Complete Medical History**	X													
**Interim Medical History**		X	X	X	X	X	X	X	X	X	X	X	X	X
**Complete Physical Exam**	X													
**Limited/Directed Physical Exam ***		X	X	X	X	X	X	X	X	X	X	X	X	X
**Physical Activity History**		X	X	X	X	X	X	X	X	X	X	X	X	X
**Pregnancy inquiry (as appropriate)**	X	X	X	X	X	X	X	X	X	X	X	X	X	X
**Prior/Concomitant Meds**	X	X	X	X	X	X	X	X	X	X	X	X	X	X
**Adverse Event Assessments**	X	X	X	X	X	X	X	X	X	X	X	X	X	X
**Daily Insulin U/kg/day, Type of Insulin**	X	X	X	X	X	X	X	X	X	X	X	X	X	X
**Severe Hypoglycemia History**	X	X	X	X	X	X	X	X	X	X	X	X	X	X
**Clinic POC HbA1c**	X				X			X			X			X
**Control Group Months 0–6: Libre Pro (blinded) CGM placed in clinic and returned to clinic the following month, test strips dispensed in clinic and SMBG downloaded monthly ****		X	X	X	X	X	X							
**CGM Group Months 0–12 and Control Group Months 7–12: Libre 2 (unblinded) CGMs dispensed in clinic monthly, worn continuously, and completed CGMs returned monthly to clinic**		X	X	X	X	X	X	X	X	X	X	X	X	
**Insulin Dispensed**		X	X	X	X	X	X	X	X	X	X	X	X	X
**Validated Questionnaires *****	X							X						X
**Patient Education**	X	X	X	X	X	X	X	X	X	X	X	X	X	X

* monthly physical exam, ** done monthly for 6 months, *** Questionnaire filled every 6 months.

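### The primary cost endpoint is a modelled supply list with one value per arm, yet section 2.8.3 sends it to a two-sample test and a regression, which cannot be applied to it

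*Protocol article*

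**What the plan says.** The abstract names two primary endpoints, the second being "2) a cost analysis of CGM versus SMBG". It says that the assumptions cover direct material costs and also indirect ones: hospital stays, missed school or work, and complications.

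Section 2.8.2 is narrower. It carries the label "Primary cost analysis: material cost of the Libre CGM system vs. SMBG" and describes a supply list. For SMBG it states "We calculated the cost of three times daily SMBG per patient per 1 year", from inputs such as "3 test strips per day per patient plus 10% for supplementing those who might need additional support" and "one glucometer per patient per year plus a replacement in up to 20% of patients in the second half of the year". For CGM it lists one reader, 26 sensors a year, confirmation strips four times a week, a lancet device and 50 lancets, and adds: "We assume 10% extra of these supplies for replacement or increased needs, except for sensors, where we assume 20% extra are needed". The calculation is reported in the past tense, although section 3 says the third of four cohorts is still in progress.

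Costs worked out for each patient (admissions for severe hypoglycemia and DKA, days missed) appear only in section 2.8.3, under the secondary cost analyses. The last paragraph of that section first promises summary statistics for every cost endpoint. It continues "The primary and secondary endpoints will be compared between the CGM and SMBG groups using 2-sample" t-tests or Wilcoxon rank-sum tests, and adds linear regression adjusted for covariates such as age, gender and education.

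**The concern.** A two-sample test compares a difference with the spread between patients. The primary cost in 2.8.2 has no such spread: it is a price list multiplied by assumed quantities, and every patient in an arm would carry the same figure. A p-value from it would say nothing about whether the cost gap is large or robust. What is uncertain is the unit prices, the replacement shares and the spare allowances, and none of these enters the test. The regression has the same fault, because age, gender and education cannot explain a constant.

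Cost is one of two primary endpoints, and section 2.9 says the findings go to the Ministry of Health to inform policy. A vanishing p-value beside the material-cost figure could present assumed allowances as trial evidence.

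**Working it through.** **Plan's own figure.** The article gives no cost estimate, sample size or power for the cost endpoint, so there is none to reproduce. The group sizes used here come from section 2.7: 180 randomised (90 per arm), and 180 × 0.80 = 144 completing (72 per arm).

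**Step 1. What the list produces per patient-year (2.8.2).**

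| Item | SMBG three times daily | CGM |
|---|---|---|
| Strips | 3 × 365 × 1.10 = 1,204.5 | 4 × 52 × 1.10 = 228.8 |
| Sensors | none | 26 × 1.20 = 31.2 |
| Meter or reader | up to 1 + 0.20 = 1.2 | 1 × 1.10 = 1.1 |
| Lancet device | up to 1 + 0.50 = 1.5 | 1 × 1.10 = 1.1 |
| Lancets | 2 × 200 = 400 | 50 × 1.10 = 55 |

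Fractional meters and sensors show that these are averages from a model, not counts for a person. Multiplied by prices, they give one number per arm.

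**Step 2. The t-test.** t = (difference in means) / (SD × √(2/n)). With SD = 0 in both arms the denominator is zero and t is undefined. Software may print p = 0, but that is an artefact.

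**Step 3. The Wilcoxon test.** With n identical values in each arm and any non-zero gap, separation is complete. U differs from its mean by n²/2. The tie-corrected variance is

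(n²/12) × [(2n + 1) − (n² − 1)/(2n − 1)] = n⁴ / [4(2n − 1)].

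With the continuity correction, z = √(2n − 1) × (1 − 1/n²).

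- n = 72: z = √143 × (1 − 1/5,184) = 11.96, two-sided p ≈ 6.0e-33.
- n = 90: z = √179 × (1 − 1/8,100) = 13.38, two-sided p ≈ 8.2e-41.

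The size of the gap does not appear in the formula. Running the test on constant groups with gaps of 0.01, 1 and 100 currency units gave the same p-value each time.

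**Step 4. The regression.** With one value per arm, a group indicator fits perfectly and the residual variance is zero. Standard errors and covariate effects carry no information.

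**Step 5. Where the uncertainty lies.** Ten points of sensor allowance is 26 × 0.10 = 2.6 sensors per patient-year, and 2.6/31.2 = 8.3% of the assumed sensor quantity. This shows how the figure responds to an assumption; it does not show that 20% is wrong.

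**Step 6. If replacements did vary by patient.** Suppose that 20% of SMBG patients replace a meter and 50% a lancet device, independently, and that the CGM arm is constant. Unit prices are not in the article, so I assume a range. SD = √(meter² × 0.2 × 0.8 + device² × 0.5 × 0.5).

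- Meter 10, device 2: SD = √(16 + 1) = 4.1. A gap of 1.96 × 4.1/√72 ≈ 1 unit reaches two-sided p = 0.05.
- Meter 50, device 10: SD = √(400 + 25) = 20.6. The corresponding gap is 1.96 × 20.6/√72 ≈ 5 units.

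The test would then be defined, but its variance would come only from minor items. Strips and sensors would still be constants.

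**The case against.** The strongest reply is that the planned methods presuppose patient-level costs, so the authors may intend them. Some items in 2.8.2 fall on some patients and not others (meter and lancet-device replacement, extra strips), and the article never says that each participant will be assigned the average. The abstract includes indirect costs, which 2.8.3 does work out per patient. An endpoint built that way would have variance and could be tested. The derivation may also be set out in a fuller document that is not shown.

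Part of this stands: zero spread is an inference from the list. It does not remove the problem. Section 2.8.2 labels material cost alone as the primary cost analysis, treats the replacement shares as assumed upper limits and names no recorded use. If the abstract's wider definition is meant, 2.8.2 is inconsistent with it and the two must be reconciled. Reading the word primary as meaning TIR does not help either: the sentence closes the cost plan, follows a sentence about cost endpoints, and TIR has its own mixed model in 2.8.1.

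Three stronger readings are tempting but not supported:

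- **That the t-test would declare any price gap significant.** It is undefined; only the Wilcoxon test returns a tiny p-value.
- **That the strip cost is overstated because patients may test less often.** Section 2.8.2 costs supplies provided, and controls are given enough for three tests a day. A lower use rate would be an outside assumption and would not show an error in a provision cost.
- **That costing each patient's actual use could replace the model.** Controls switch to CGM after month 6, so a one-year SMBG cost is never observed, including the replacements placed in the second half of the year. Table 1 also lists no record of meter, reader or lancet replacement.

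**Conclusion.** The concern holds as a mismatch between a modelled endpoint and an inferential test. Followed as written, 2.8.3 applies to a primary endpoint a t-test that is undefined, or a Wilcoxon test whose p-value (about 6e-33 at 72 per arm, 8e-41 at 90) reflects only the number of patients. This rests on reading 2.8.2 literally, with one modelled value per arm. If patient-level costs are intended, the sections still need reconciling, because 2.8.2 does not define such an endpoint.

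A reader might infer that the cost results as a whole are invalid. The documents do not support that: the modelled figures can stand as a budget calculation, the per-patient secondary costs can be tested, and randomisation, data collection and the TIR analysis are unaffected. Should-fix.

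**What to change.** 1. In 2.8.3, restrict the t-test, Wilcoxon and regression sentences to costs measured per patient (admissions, missed school or work).
2. Report the modelled material cost difference as a deterministic figure, with a sensitivity range over unit prices and over the replacement and spare allowances.
3. Reconcile the abstract with 2.8.2, stating whether the primary cost endpoint is material cost alone or includes indirect costs.
4. Optionally, as a supportive analysis, cost the sensors and strips recorded per patient in months 0–6 by randomised arm, and report the mean difference with an interval. Table 1 already has "Libre 2 (unblinded) CGMs dispensed in clinic monthly, worn continuously, and completed CGMs returned monthly to clinic", and for controls it has strips dispensed and meters downloaded monthly. It lists strip dispensing only in the control row, so check whether the CGM arm's confirmation strips are logged. Leave out the controls' blinded sensors, which serve endpoint assessment. Label the result a six-month consumables cost that supplements the one-year model and does not replace it.

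Items 1 to 3 are short text changes plus a sensitivity table. Item 4 is a tabulation of dispensing records, as far as they are kept per patient. No new visits or procedures are needed. Section 3 puts last follow-up in April 2027, so the change can precede the final analysis.
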